#### Interim and Subgroup Analyses

No interim analyses are conducted. As the literature suggests possible differences in outcomes based on sex, gender, race, and ethnicity [112-114], we examine sex, gender, race, and ethnicity as moderators of group effects. We also examine whether there are facilitator effects (eg, effects of a particular MBRP facilitator) by incorporating the facilitator as a random effect in the mixed effects models. We also test whether addiction cycle domains moderate the association between MBRP and primary and secondary outcomes.

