MBRP groups are facilitated by experienced community clinicians and clinical psychology graduate students. Facilitators were trained by SB and KW, who have trained MBRP facilitators for the past 2 decades. All MBRP facilitators are required to have a personal mindfulness practice and experience with mental health or addiction counseling. Many groups are cofacilitated with 2 or more facilitators and all facilitators receive group supervision from SB. The MBRP sessions are audio-recorded and uploaded to REDCap. Fidelity ratings of all group sessions are completed by a trained research coordinator and 10% of sessions are randomly selected for double coding by a trained graduate student or research assistant. Treatment fidelity is assessed using an adapted version of the Mindfulness-Based Relapse Prevention Adherence and Competence Scale (MBRP-AC) [65]. MBRP facilitators (n=15) are also invited to participate in the qualitative evaluation of the program.

To support group engagement and attendance, MBRP group attendees are provided weekly and monthly reminders of MBRP group times and any updates (eg, cancellations due to holidays). Groups are flexible, offered based on patient availability and interest such that new group times are formed to better accommodate participant schedules.

**Table 1. T1:** MBRP^a^ session content.

Session	Content
1	Eating meditation with a small piece of food (eg, dried fruit), introduction to the SOBER^b^ breathing space, and using mindfulness in daily life
2	Mindfulness of thinking and thoughts, breath meditation
3	Mindful movement, SOBER breathing space, mindfulness, and valued living
4	Body scan, developing a daily practice and common challenges therein, false refuge
5	Kindness practice
6	SOBER breathing space in a challenging situation
7	Mindfulness and acceptance of difficult emotions, the Guest House poem meditation, and reading
8	Urge surfing

a MBRP: mindfulness-based relapse prevention.

b SOBER: Stop-Observe-Breathe-Expand-Respond.

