#### Referral to Online Mutual Support Condition

The orientation session for the referral group is the only intervention provided to the comparator group, consisting of an orientation to online mutual support programs: InTheRooms, AA online, and SMART Recovery. Referral sources for individuals who are in crisis (eg, calling 988) are offered, as well as information about optional mobile apps for those wanting mobile app support (eg, apps to track drinking).

Mutual support groups are free, peer-led organizations designed to help individuals with substance use disorders and other addiction-related problems. Mutual support groups often focus on communication and exchange of addiction and recovery experience and skills. Through shared activities and discussions, participants provide mutual support and learning among individuals facing similar challenges.

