### Sample Size Considerations

Based on prior experience modeling outcomes over time and examining differences between MBRP and comparison groups, we are interested in powering the study to detect a small effect size difference between MBRP and referral to online mutual support in supporting recovery (primary outcome). We estimate power based on our prior efficacy trial [44] in which the difference at 12 months posttreatment on cessation of heavy drinking between MBRP and treatment as usual was a Cohen h=0.36. With a 2-tailed α of .05 and 430 participants (215 per group), we anticipate power greater than .90 to detect a similar effect size. To further ascertain power for the proposed set of analyses, Monte Carlo simulation studies were conducted to estimate power for testing the secondary outcomes given the proposed modeling approaches and likely parameter estimates. Power is greater than .90 for examining the effects of MBRP versus referral to mutual support on secondary outcomes over time. Given the use of modern missing data handling techniques [84,85] and an intent-to-treat design, we do not need to adjust sample size for potential attrition in the trial, although we aim to have 80% retention across the trial.

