### Statistical Methods

#### Primary Outcome Analysis

We use a generalized linear mixed model (GLMM) that can accommodate a binary outcome (recovery vs not recovery as defined by the NIAAA definition [17]) and random effects that correct for the nonindependence of repeated measures in longitudinal data to assess within-person change over time. The recovery binary variable is created using the 3 indicators included in the definition at each time point. AUD remission is based on not endorsing criteria for AUD (other than craving which may persist even during abstinence), cessation of heavy drinking is defined by no self-reported heavy drinking days, and improvements in functioning and well-being as measured by higher score (from baseline) on the WHOQOL-BREF [68] domain scores (each of 26 items scored from 1 to 5 on a response scale, which are then transformed linearly to a 0‐100 scale) and the 36-item Short Form Health Survey [69] Mental Health Component Score (scored on a 0‐100 scale). The analyses consist of estimating a GLMM with fixed effects of baseline sociodemographics and covariates used in randomization (sex and AUD severity), fixed effects of random assignment to MBRP versus online mutual support referral, and random effects of time.

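### The confirmatory model leaves out MBRP-arm clustering by facilitator or group; if outcomes correlate within these clusters, its standard error will be too small

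*Protocol article*

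**What the plan says.** All references are to the protocol article.

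- **MBRP Condition.** Treatment is given in rolling, facilitator-led groups, and participants may attend as often and for as long as they wish. "Many groups are cofacilitated with 2 or more facilitators".
- **Referral to Online Mutual Support Condition.** The individual orientation session "is the only intervention provided to the comparator group". Any mutual support group that a referral participant then joins is outside the study and self-chosen.
- **Primary Outcome Analysis.** The generalized linear mixed model has "random effects that correct for the nonindependence of repeated measures in longitudinal data". The listed terms are baseline sociodemographics, sex, AUD severity, randomized arm and random effects of time. No group or facilitator term is named. Secondary Outcome Analyses describes its models in the same way.
- **Interim and Subgroup Analyses.** The authors will examine whether facilitator effects exist by "incorporating the facilitator as a random effect in the mixed effects models". Group is not given a random effect anywhere.
- **Sample Size Considerations.** With "430 participants (215 per group") and a two-sided alpha of .05, the authors write: "we anticipate power greater than .90 to detect a similar effect size". The effect is taken from a prior trial, where the difference "between MBRP and treatment as usual was a Cohen h=0.36". No clustering or ICC is mentioned.

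**The concern.** Participants who share a facilitator or a group may come to have similar outcomes, because they share the facilitator's skill and one another's company. The design creates this dependence in one arm only. A model with person-level random effects treats all participants as independent of one another, so it would overstate the information in the MBRP arm.

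The article does not overlook facilitator effects, but it places them in an exploratory section where they do not protect the confirmatory test. At stake are the type I error of the primary comparison, the width of its interval, and a power statement that assumes independent participants.

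A separate look for facilitator effects is also a weak safeguard, since clustering affects the standard error whether or not it is detected.

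**Working it through.** **Inputs from the article:** 215 per group, two-sided alpha 0.05, h = 0.36.

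**Assumed, because the article does not give them:** an ICC of 0.01 to 0.05, and 15 equal clusters in the MBRP arm. The figure of 15 is the number of facilitators invited to the qualitative evaluation (MBRP Condition) and serves only as an indication.

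**Step 1. Reproduce the stated power.** Power = Φ(h·√(n/2) − 1.96) = Φ(0.36 × √107.5 − 1.96) = Φ(3.73 − 1.96) = 0.962. This agrees with the stated figure of more than .90.

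**Step 2. Add clustering in the MBRP arm only.**
- Cluster size m = 215/15 = 14.3.
- Design effect in the MBRP arm: DE = 1 + (m − 1) × ICC. In the referral arm it is 1.
- Ratio of true to naive standard error: R = √((DE + 1)/2).
- True type I error of the naive test: 2 × (1 − Φ(1.96/R)).
- Power when the correct standard error is used: Φ(0.36 × √107.5 / R − 1.96).

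| ICC | DE | R | True type I error | Power |
|---|---|---|---|---|
| 0 | 1.000 | 1.00 | 5.0% | 0.962 |
| 0.01 | 1.133 | 1.03 | 5.8% | 0.951 |
| 0.02 | 1.267 | 1.07 | 6.6% | 0.939 |
| 0.05 | 1.667 | 1.15 | 9.0% | 0.898 |

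**Step 3. Vary the cluster assumption.**
- *30 clusters* (m = 7.2), ICC 0.05: DE = 1.308, R = 1.07, true error 6.8%, power 0.935.
- *Half of the MBRP arm attends no group.* The other half is spread over 15 clusters, m = 107.5/15 = 7.2. At ICC 0.05 the attenders have DE 1.308 and the rest have 1, so the arm average is (1.308 + 1)/2 = 1.154. Then R = √(2.154/2) = 1.04, true error 5.9%, power 0.949.

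**Step 4. Would a separate facilitator check reveal the problem?** Take a 5% one-way variance test on a continuous outcome, 215 participants and 15 facilitators. The chance of detection is P(F > F_crit/(1 + m·ICC/(1 − ICC))) with 14 and 200 degrees of freedom. This gives about 11%, 18% and 46% at ICC 0.01, 0.02 and 0.05. A binary outcome should do no better.

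These are equal-cluster, single-time-point approximations on the arcsine scale. They show direction and rough size and do not simulate the longitudinal model.

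**The case against.** The strongest counter-argument is that the effect is conditional and may be small. A reader might infer that the primary standard error *is* too small. The documents do not support that: they give no ICC, and at ICC 0 nothing changes. At 0.01 with 15 clusters the shortfall is about 3%. This objection stands, and the point is worded accordingly.

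The cluster count is also unconfirmed. Study Setting says that facilitator participants are a subset of the MBRP facilitators, so the number who treat may exceed 15. The modified intent-to-treat set requires only the individual orientation session, so some MBRP participants may never join a group. Rolling attendance and cofacilitation spread each person over several clusters. All of this tends to dilute the effect, as Step 3 shows. Scenarios with only a handful of clusters or an ICC of 0.10 would look more alarming but have no source in the article.

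A reader might also infer that the planned facilitator term is an ordinary random intercept that would miscode referral participants, who have no facilitator. The article says only that it is a random effect. Its coding is a matter for the analysis plan, which is not shown, and is not criticised here.

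Finally, the plan is not silent, since a model with facilitator will be fitted. But the article lists the terms of the primary model and states what its random effects are for, and it puts facilitator elsewhere as something to examine. On that wording the facilitator model is not the confirmatory one. This part of the concern survives.

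**Conclusion.** The point holds in conditional form. The confirmatory model, as described, makes no allowance for clustering that the design creates in one arm. Any positive correlation within facilitator or group makes its test anticonservative.

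Under the assumption of 15 equal clusters and ICC 0.01 to 0.05, the standard error should be 3% to 15% larger, the true type I error is 5.8% to 9.0%, and power is 0.95 to 0.90. The power claim largely survives and becomes marginal only at the upper end of that range. The type I error is the greater concern. With more clusters or many non-attenders the inflation is smaller, about 6% to 7% at ICC 0.05 in the cases shown. The correction is worth making because follow-up is still under way and the analysts are blinded, so the model can be settled before the outcome comparison is seen.

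**What to change.** 1. Move the facilitator random effect (or one for the most-attended group) from the subgroup section into the primary model, as a partially nested term that acts in the MBRP arm only. State that referral participants, and MBRP participants who attended no group, are treated as singletons.
2. Use small-sample inference suited to the modest number of clusters.
3. Add a multiple-membership model as a sensitivity analysis, because groups are rolling and many are cofacilitated.
4. In Sample Size Considerations, state power over an assumed ICC range of 0.01 to 0.05.

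**Cost.** The interval will be somewhat wider and the stated power slightly lower. There is some extra modelling work, because a binary mixed model with small-sample inference has to be fitted in each of the 100 imputed datasets. Attendance data are collected, but the article does not say that facilitator is recorded for each participant and session. That should be confirmed first.

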#### Analysis Approach and Missing Data

Primary analyses are performed under the modified intent-to-treat (mITT) principle, whereby each eligible participant is analyzed according to the intervention group to which they were assigned at the time of randomization. Moreover, the mITT sample excludes participants who never attended the orientation session or those who were deemed ineligible after randomization. The rationale for using the mITT sample in primary analyses is to address the fact that some participants, in either randomization group, do not initiate treatment. The ITT estimates the effect of the assigned treatment and is biased toward the null to estimate the effect of the intervention (in the absence of noninitiation). The mITT estimator is appropriate because (1) noninitiation is identifiable in each group and (2) it is reasonable to assume that if someone does not initiate treatment in one arm, they would also not initiate treatment in the other arm; in fact, both arms begin with the same introductory orientation session.

Additionally, we conduct a per-protocol analysis that includes only participants who attend at least 2 sessions of the MBRP groups or correspondingly attended at least 2 mutual help group sessions. The per-protocol analysis excludes participants who did not attend at least 2 intervention sessions or those who were deemed ineligible after randomization.

Multiple imputation is used to accommodate missing outcome data [115]. We test missing data assumptions using sensitivity analyses [85,116]. We generate 100 imputed datasets, fit the primary analysis model to each imputed dataset, and combine the results by using Rubin rules.

#### Data Sharing

Sharing of data is germane to the advancement of science and medicine for the public good. This study will comply with all applicable NIH Data Sharing Policies. The investigators comply with all NIAAA Data Archives policies established during the project period. This includes compliance with the NIAAA central data platform requirements and timelines developed through the NIAAA Data Share. Institutions that receive Data and/or Materials from this award for performance of activities under this award are required to use the Data and/or Materials only as outlined by the NIAAA Data Share in a manner that is consistent with applicable state and federal laws and regulations, including any informed consent requirements and the terms of the institution’s NIH funding, including NOT-OD-17‐109 and 42 U.S.C. 241(d). A releasable database is produced and is completely deidentified in accordance with the definitions provided in HIPAA. Namely, all identifiers are recoded in a manner that will make it impossible to deduce or impute the specific identity of any participant. The database does not contain any institutional identifiers.

The study established a Data Safety Monitoring Board (DSMB) in the first year of the trial, composed of 3 established investigators external to the study. DSMB members are provided with annual reports of progress in the study, including information about screening (inclusion and rate of exclusion), demographics, and adverse events data. The committee uses these reports to decide whether we can continue recruitment, propose a protocol amendment, or stop recruitment for the trial. Severe adverse events are reported immediately to the DSMB. The DSMB members are then asked to make a recommendation regarding continuing the study, scheduling a formal meeting to discuss the event, or immediately stopping the study. If any members of the DSMB request a meeting, then the PI schedules a formal meeting within 1 week of the request. At the meeting, the DSMB holds a vote on whether the study should (1) continue unchanged, (2) make a protocol amendment, or (3) stop recruitment. If any DSMB member requests a protocol amendment or discontinuation of the study, the PI informs the IRB and funding agency immediately.

It is the responsibility of the PI, KW, to obtain and maintain approval of all procedures from the UNM. On a regular basis, the research team reports on the procedures being used in the protocol to ensure that all IRB-approved procedures are being followed. Any adverse events are reported to the PI immediately. Serious adverse events and unanticipated problems are reported to the local IRB and funding agency (NIAAA) project officer within 48 hours. In addition, the study PI prepares a summary of the DSMB report to NIAAA annually as part of the progress report. There are no plans for auditing trial conduct, although the UNM IRB could decide to audit the trial at any time. Protocol modifications are reported to the local IRB, DSMB, and NIH ClinicalTrial registry.

#### Dissemination

We registered the trial with ClinicalTrials.gov and provided an informational website through the CASAA. Informed consent documents for the trial include a specific statement relating to the posting of clinical trials information on ClinicalTrials.gov. All clinical trials registration and reporting of results occur in compliance with the policies of the UNM and the NIH.

We expect to present preliminary results at scientific meetings, including the Collaborative Perspectives of Addiction, Research Society on Alcohol, and Society for Implementation Research Collaboration. All results are disseminated through published manuscripts and presentations at scientific meetings. After the primary results have been published, the database will be cleaned and purged of identifiers and made available to researchers for secondary analyses via the NIAAA Data Archive.

## Results

Funding for this study was awarded by the NIAAA (R01AA031159, PI: [name]) in August 2023. The version date for the latest protocol is December 22, 2025, and this is version 3.0 of the Protocol. Protocol changes included adding measures, adding an initial screening form online (vs via phone), increasing sample size, and adding procedures for participants to be recruited by other researchers. Recruitment began on September 13, 2023, and the last recruited participant was randomized on March 20, 2025. We randomized 470 individuals, of whom 432 completed orientation sessions, just going past the trial target of n=430 (100.5% recruited). The 6-month data collection has also been completed for all participants, and 369 completed the 6-month follow-up, 34 withdrew from the study prior to the 6-month follow-up; thus, the follow-up completion rate among those who continued in the study was 369/436 (86%) and the overall follow-up rate for all randomized participants was 369 out of 470 (78.5%).

## Discussion

### Principal Findings

This paper describes a hybrid type 1 effectiveness-implementation design to prospectively test the effectiveness of MBRP and to identify barriers and facilitators of group participation to inform future implementation of MBRP as continuing care. We hypothesize that MBRP may support longer-term recovery from AUD via a broader focus on whole-person functioning and by targeting addiction domain cycles.

### Limitations and Strengths

There are several design considerations that should be highlighted. First, we chose a 2-group design and will not randomize to different kinds of mutual support (eg, SMART Recovery vs AA). In our initial power analyses, we found that including another randomization group would more than double the required sample size. Second, we opted not to directly recruit from specific treatment programs and to partner with specific AUD treatment programs, and to also include those who make changes in the absence of treatment. We view this as a limitation and a strength. Although we collect information about the amount and type of treatment received (via the treatment history form), we are relying on self-report and we are not able to objectively assess whether specific AUD treatments, as actually delivered by the treatment programs, are associated with recovery outcomes. This design decision is also a strength in that the findings may generalize to a number of different treatment programs or those who make changes without treatment. Thus, the study assesses the effectiveness of MBRP as continuing care regardless of how people make initial changes in their drinking (through treatment or self-change). Finally, self-reported drinking and drug use measured retrospectively via the Timeline Followback has limitations [122]. It would be impossible to quantify pre-baseline levels of drinking and drug use with any other method and quantifying within-person change in drinking and drug use is critical for our aims and hypotheses. We have included PEth to biochemically assess drinking at baseline and 3-year follow-up.

### Future Directions

If our hypotheses are supported, findings would set the stage for several avenues for future research and widespread dissemination, including the communication of findings within conference presentations and peer-reviewed manuscripts, as well as making the MBRP via Zoom manual, orientation materials, participant worksheets, and facilitator training materials publicly available. This would serve to expand continuing care options and provide an alternative for individuals who are seeking non–abstinence-based recovery support.
